**11.4.2.18 Korean version of Pittsburgh Sleep Quality Index (PSQI-K)**

The PSQI-K consists of 19 self-reported questions and 5 questions for the roommate or bed partner. Only the 19 self-reported questions are used to calculate the global score, which ranges from 0 to 21. Seven component scores are derived from the 19 questions, and the global score is the sum of these component scores.

#### **11.4.2.19 Korean-Montreal cognitive assessment (K- MOCA)**

Although the K-WAIS-IV is a good tool for comprehensively assessing cognitive function, it takes more than an hour per evaluation, making it challenging for repeated assessments. Therefore, the K-MOCA, a simpler tool that is more sensitive to cognitive decline than the MMSE, is used. K-MOCA includes visuospatial ability, executive function (3 points), language ability - vocabulary (3 points), language ability - sentence construction (3 points), attention (6 points), calculation (2 points), and orientation (6 points). Memory is included but not scored. The total score is 30 points, with a score of 23 or higher considered normal cognitive function.[30] .

#### **11.4.2.20 Becks' depression inventory (BDI)**

This inventory assesses the presence and severity of depressive symptoms following COVID-19 infection or recovery. It consists of 21 items covering cognitive, emotional, motivational, and physical symptoms of depression, with a total score range of 0-63. Higher scores indicate more severe depressive symptoms.[31] [32] .

#### **11.4.2.21 Digit Span Test (Forward and Backward)**

The Wechsler intelligence scale, widely used in clinical settings, includes the digit span subtest, which is a simple tool to assess cognitive decline, short-term memory, and working memory. In the digit span test, the examiner reads a series of numbers, and the subject repeats them in the same order (DF) or in reverse order (DB). DF ranges from 3 to 9 digits, and DB ranges from 2 to 8 digits. The test is stopped if the subject fails twice consecutively. The score is the highest number of digits correctly repeated, with separate scores for DF and DB. High scores indicate good short-term memory, and a DF-DB score difference of 5 or more indicates abnormal working memory. [44] .

#### 11.4.2.23 Short Physical Performance Battery (SPPB)

The Short Physical Performance Battery (SPPB) is a test that assesses the physical function of elderly individuals or those with post-illness frailty. It comprises three tests: static balance test, gait speed test, and chair stand test. It is administered to evaluate the decline and recovery of physical function in patients with chronic COVID-19 syndrome. The specific methods are as follows:

**Static Balance Test:** This test evaluates balance in three postures: side-by-side, semi-tandem, and tandem. The subject is required to maintain each posture without losing balance for 10 seconds. The maximum score is 4 points. Successfully maintaining the side-by-side and semi-tandem postures earns 1 point each. For the tandem posture, maintaining it for 10 seconds earns 2 points, for 3-9.99 seconds earns 1 point, and for less than 3 seconds earns 0 points.

**Gait Speed Test:** This test measures the time taken to walk a distance of 4 meters. The maximum score is 4 points. Completing the walk in less than 4.82 seconds earns 4 points, 4.82-6.20 seconds earns 3 points, 6.21-8.70 seconds earns 2 points, more than 8.70 seconds earns 1 point, and inability to walk earns 0 points.

**Chair Stand Test:** This test measures the time taken to stand up from a chair five times using only the leg muscles, without the aid of arms. The maximum score is 4 points. Completing the task in less than 11.20 seconds earns 4 points, 11.20-13.69 seconds earns 3 points, 13.70-16.69 seconds earns 2 points, more than 16.70 seconds earns 1 point, and inability to complete five stands or taking more than 60 seconds earns 0 points.

In this study, the Andante Fit system is used for precise measurement. The Andante Fit consists of a gait speed measurement device, a chair stand measurement device, and a static balance measurement device. The system takes 2-3 minutes to complete the measurements, and scores for each item and the total score are automatically generated upon completion. [35] .

|                            |                         |
|----------------------------|-------------------------|
| Composition of Andante Fit | Example of test results |
|----------------------------|-------------------------|

[figure not shown]

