## **7 . Subject selection**

### **1) Inclusion criteria**

- Adults aged 19 and above who have been diagnosed with COVID-19 for at least 12 weeks.
- Individuals who have experienced fatigue for more than 4 weeks that was not present before their COVID-19 diagnosis.
- Individuals with an FSS score of 4 or higher.
- Individuals with no significant cognitive impairments who voluntarily consent to participate in the study through written consent.

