**15.1.2 Secondary evaluation variables**

- 1) Final medication adherence  
: The mean, standard deviation, median, minimum, and maximum of the final medication adherence (%) for all subjects after 12 weeks (visit 4 or end of the study) will be presented.
- 2) Differences in final medication adherence between groups  
: The mean, standard deviation, median, minimum, and maximum of the final medication adherence (%) will be calculated and compared between the two groups after 12 weeks of intervention (visit 4 or end of the study).
- 3) FSS scores at visits 2 and 3  
: The FSS scores at each visit will be compared between groups.
- 4) ChFS scores and subscale scores at visits 2, 3, and 4  
: The total score and the subscale scores for physical (items 1-7) and mental health (items 8-11) will be recorded. The total scores and subscale scores at each visit will be calculated and compared between the groups.
- 5) EQ-5D-5L scores at visits 2, 3, and 4  
: The EQ-5D-5L scores will be calculated, and the scores at each visit will be compared between the groups.
- 6) PSQI-K global scores at visits 2, 3, and 4  
: The scores for the 7 components from the PSQI-K questionnaire will be calculated and summed to determine the Global score. The Global scores at each visit will be compared between the groups.
- 7) K-MOCA total and domain scores at visit 4  
: The scores for the 7 domains will be calculated and summed to determine the total score. The total scores will be compared between the groups at visit 4.
- 8) BDI score at visit 4  
: The scores for the 4 domains will be summed to determine the total score, which will be compared between the groups at visit 4.

- 9) DF score, DB score, DF-DB scores at visit 4  
: These scores will be compared between the groups at visit 4.
- 10) Computerized neurocognitive test scores at visit 4  
: The scores for the 5 computerized neurocognitive tests will be compared between the groups at visit 4.
- 11) SPPB test scores for walking Speed, sit-to-stand test, balance test, and total score at visit 4  
: The scores for these 3 tests and the total score will be compared between the groups at visit 4.
- 12) Analysis of recruitment rate, enrollment rate, dropout rate, and reasons for dropout for feasibility evaluation  

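### The SPPB is analysed only as capped 0-4 scores and their total, so improvement beyond the cut-offs cannot register; add gait speed and chair-stand time

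*Protocol*

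**What the plan says.** Section 11.4.2.23 introduces the SPPB as a test that "assesses the physical function of elderly individuals or those with post-illness frailty" and says it is used here to follow decline and recovery of physical function in chronic COVID-19 syndrome. There are three tests, each with a maximum of 4 points:

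- Gait: "This test measures the time taken to walk a distance of 4 meters". "Completing the walk in less than 4.82 seconds earns 4 points".
- Chair stand, five repetitions: "Completing the task in less than 11.20 seconds earns 4 points".
- Balance: one point each for the first two postures, then "For the tandem posture, maintaining it for 10 seconds earns 2 points".

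The Andante Fit device is used, and "scores for each item and the total score are automatically generated upon completion".

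The outcome is fixed as these scores in the protocol summary, in section 14.3.2 and in section 15.1.2 item 11: "The scores for these 3 tests and the total score will be compared between the groups at visit 4". No section names walking time, gait speed or chair-stand time as an outcome. Section 14.1 prescribes ANCOVA on the baseline value, with Ranked ANCOVA if assumptions fail or outliers appear.

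Entry is open to "Adults aged 19 and above who have been diagnosed with COVID-19 for at least 12 weeks" with an FSS score of 4 or higher. Section 7 sets no limit on mobility, frailty or SPPB score.

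**The concern.** A score that stops at 4 treats everyone beyond the cut-off alike. The instrument is described for elderly or frail people, while the trial admits any adult from 19 and excludes several chronic diseases, so some participants may start at the maximum. They can get worse on the score, but they cannot get better.

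In the Schedule Summary the SPPB is the only performance-based test of physical function; the other functional measures are cognitive tests or questionnaires. The pilot is meant to inform the design of later studies and to size a confirmatory trial. If many values tie at 4, a null SPPB result could reflect the score and be read as no effect, and the effect size and SD carried forward would be those of a truncated scale.

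**Working it through.** The protocol states no power or effect figure for the SPPB, so there is nothing to reproduce.

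**1. Where the score stops (section 11.4.2.23)**

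- Gait: 4 m / 4.82 s = 0.830 m/s.
- Chair stand: 11.20 s / 5 = 2.24 s per stand.
- Total: 4 + 4 + 4 = 12.

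**2. Share at the maximum (assumed distributions)**

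The documents give no gait speeds or chair times. The means and SDs below are assumptions, with a normal distribution, chosen to lie on both sides of the cut-offs.

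Gait share = 1 − Φ((0.830 − mean)/SD). Example, mean 1.0 and SD 0.20: 1 − Φ(−0.85) = 80%.

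Chair share = Φ((11.20 − mean)/SD). Example, mean 10 and SD 3: Φ(0.40) = 66%.

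| Mean gait speed (m/s) | Share at 4, SD 0.15-0.25 |
|---|---|
| 0.7 | 19-30% |
| 0.8 | 42-45% |
| 0.9 | 61-68% |
| 1.0 | 75-87% |
| 1.1 | 86-96% |
| 1.2 | 93-99% |

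| Mean chair time (s) | Share at 4, SD 2-4 |
|---|---|
| 8 | 79-95% |
| 10 | 62-73% |
| 11 | 52-54% |
| 12 | 34-42% |
| 14 | 8-24% |

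Under normality, a majority is at the gait maximum only if the mean exceeds 0.83 m/s, and at the chair maximum only if the mean is below 11.20 s.

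**3. Cost in power, gait test only**

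The numbers per arm (50), the ANCOVA on baseline and the two-sided 5% level come from the protocol. The gain of 0.10 m/s, SD 0.20 m/s and baseline correlation 0.7 are assumptions. Each simulated trial was analysed once on speed and once on the protocol's gait score. Ranges show the spread between repeated simulations.

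| Mean baseline (m/s) | At 4 at baseline (SD 0.20) | Power, speed | Power, score |
|---|---|---|---|
| 0.7 | 26% | 92-94% | 81-82% |
| 0.8 | 44% | 92-94% | 76% |
| 0.9 | 64% | 92-94% | 61-64% |
| 1.0 | 80% | 92-94% | 41-43% |
| 1.1 | 91% | 92-94% | 20-22% |
| 1.2 | 97% | 92-94% | 4-5% |

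**4. Does ranking help?**

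Tied maxima receive the same rank. In simulation at means of 0.9, 1.0, 1.1 and 1.2 m/s, ranking the score gave 60%, 41%, 22% and 5%, against 63%, 42%, 22% and 5% without ranking.

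**The case against.** A reader might infer that most participants will already be at the ceiling. The protocol does not show this. Section 11.4.2.5 confirms fatigue only with difficulty in at least three of four activity areas, section 25 admits people aged 65 and older, and section 11.4.2.23 gives a reason for using the test in post-illness patients. None of this shows that participants walk slower than 0.83 m/s, but it rules out treating a high baseline as known.

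A reader might also infer that a real change could not be seen at all. That is too strong. Worsening below a cut-off registers, participants under the ceiling can improve, and at an assumed mean of 0.7 m/s the gait score keeps about 81% power.

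Power was examined for gait alone. Nothing was simulated for chair stand, balance or the total, and the share at 12 on the total cannot exceed the smallest component share. Section 14.2 tabulates baseline SPPB scores, so a marked ceiling should be noticed. These limits stand.

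Using the instrument's own scoring is not an error, and nothing here requires demoting the scores to descriptive status.

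It could be said that this belongs in the statistical analysis plan. But the protocol itself fixes the outcome as scores in several places, and a later plan cannot recover times that were never recorded. Whether the CRF already holds them cannot be told from the documents.

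**Conclusion.** The point holds in limited form. The SPPB outcomes are capped scores, improvement beyond 0.83 m/s or below 11.20 s is invisible on the item concerned, and ranking does not repair this. In the simulations gait speed had more power than the gait score at every mean from 0.7 to 1.2 m/s; the gap ran from about 12 percentage points (93 − 81) to about 89 (93 − 4). Which end applies depends on a baseline distribution that the protocol does not give, and on the assumed gain, SD and correlation. The case for adding the raw measures therefore does not depend on the true mean; only the size of the benefit does.

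The SPPB is item 11 of 13 secondary items in a pilot. The primary FSS conclusion is not affected. This is a cheap improvement to a secondary outcome and not a flaw in the trial's main result.

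**What to change.** In sections 14.3.2 and 15.1.2 item 11, keep the SPPB item and total scores as planned and add between-group comparisons at Visit 4 of:

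- 4 m gait speed (m/s), by ANCOVA on the Visit 1 value;
- five-chair-stand time (s), by ANCOVA on the Visit 1 value.

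If any participant cannot complete a test, analyse that measure by the rank-based ANCOVA already planned in section 14.1, with inability assigned the worst rank. Stating this in advance avoids mixing ranked and raw values in one model.

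Record both times in the CRF at Visits 1 and 4, and report by group the share at the maximum score at Visit 1, so that a reader can judge how far the scores were able to move.

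The cost is two CRF fields for quantities the tests already measure, two further secondary comparisons, and one rule for participants unable to complete a test. Balance has no uncapped alternative in the protocol and stays as scored.

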#### 11.4.2.24 Medication compliance

The number of returned and taken medications will be investigated and recorded at each visit. If the number of returned medications and taken medications does not match the prescribed amount, the reason for the discrepancy should be recorded in the case report form. Medication adherence is evaluated as follows:

$$\text{Medication compliance (\%)} = \frac{\text{Number of medications actually taken}}{\text{Number of medications prescribed during the period}^*} \times 100$$

\* The number of medications prescribed during the period refers to the number of medications that should be taken from the initial administration to the visit immediately prior to returning the medications.

The final medication adherence is evaluated at Visit 4, combining the sum of the herbal preparations actually taken and the clinical trial medications that should have been taken during Visits 2, 3, and 4.

#### 11.4.2.25 Feasibility evaluation

To evaluate the feasibility of the study design, data will be collected on the recruitment rate (overall and by institution), dropout rate (overall and by institution), and reasons for dropout during the study period.

#### 11.4.2.26 Adverse event monitoring

Information about adverse events occurring in study participants should be reported spontaneously by the participants or their proxies and confirmed through interviews and medical examinations by the principal investigator or research staff. The investigation of adverse events includes the date of onset and resolution, severity and outcome of the adverse event, actions taken, the causal relationship with the administration of herbal preparations, and whether and how the adverse event was treated.

- Monitoring subjective and objective symptoms

The degree of adverse event manifestation through subjective and objective symptoms will be investigated during the investigator's medical examinations. The manifestation degree will be recorded according to the evaluation criteria, and the causal relationship with the medication and herbal preparations will also be assessed.

- Monitoring laboratory tests, vital signs, and other measurements

Clinically significant abnormal changes in laboratory tests, vital signs, and other measurements will be followed up until symptoms improve. Additionally, any factors that might have interfered with the test contents during the examination will be recorded through interviews.

## 12. Precautions for use of investigational medicinal products

### 12.2 CV1 (Jin Kyungok-go) and P (placebo)

#### 1. not take this medication if you:

an infant under 3 months of age (newborns, infants).

#### 2. Consult a doctor, herbal doctor, dentist, pharmacist, or herbal pharmacist before taking this medication if you:

- 1) Are currently taking other medications.
- 2) Are elderly (Generally, elderly individuals have diminished physiological functions and should take care to reduce dosage accordingly).
- 3) Have a significantly weakened stomach (may cause loss of appetite, stomach discomfort, nausea, vomiting, diarrhea, etc.).
- 4) Have symptoms of loss of appetite, nausea, or vomiting (symptoms may worsen).
- 5) Are an infant under 1 year of age (newborns, infants).

#### 3. Discontinue this medication immediately and consult a doctor, herbal doctor, dentist, pharmacist, or herbal pharmacist if:

bring this information leaflet when consulting.

1) You experience any of the following symptoms after taking this medication:

(1) Skin: Rash, hives, etc.

(2) Digestive system: loss of appetite, stomach discomfort, nausea, vomiting, diarrhea, etc.

2) Your symptoms do not improve after several days of taking the medication.

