## 11 . Research method

### 11.1 Research design

Patients will undergo a screening process to determine their eligibility after receiving a detailed explanation of the clinical trial and signing the consent form. Eligible patients will be randomly assigned to the treatment group (CV1, Jin Kyungok-go) or the control group (placebo) and will receive the respective intervention for 12 weeks. Each participant will visit the study site monthly during the intervention period and will undergo symptom evaluation and specimen collection (e.g., blood samples) after the 12-week intervention period, at which point the study will conclude. Recruitment will be conducted through internal and external advertisements.

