#### 11.4.1.2 Visit 1 ( start of intervention , Week 1)

If all tests and eligibility assessments are completed during the screening visit, Visit 1 can be conducted on the same day to assign participant numbers. If the screening visit and assignment of participant numbers occur on the same day, overlapping evaluations are performed only once.

- ① Measure vital signs.
- ② Investigate past and current medical history (changes between Visit 0 and Visit 1).
- ③ Assign random numbers.
- ④ Prescribe a four-week supply of the assigned herbal medicine based on the random number.
- ⑤ Participants follow the investigator's instructions for the following evaluations:
  - Assess fatigue severity using a 0-100 VAS.
  - Evaluate fatigue using the Chalder Fatigue Scale (ChFS).
  - Assess quality of life using EQ-5D-5L.
  - Evaluate sleep status using PSQI-K (Korean version of the Pittsburgh Sleep Quality Index).
  - Conduct cognitive function tests using K-MOCA (Korean-Montreal Cognitive Assessment).
  - Evaluate depression using Beck's Depression Inventory (BDI).

- Perform digit span tests (forward and backward).
- Conduct computerized neurocognitive function tests.
- Perform the Short Physical Performance Battery (SPPB).

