#### **11.4.1.3 Visits 2 and 3 (mid-term visit, Week 4 ( 28 days) $\pm 2$ days, Week 8 ( 56 days) $\pm 2$ days)**

The following tests are conducted during mid-term visits:

- ① Measure vital signs.
- ② After collecting the prescribed herbal medicine from the previous visit, verify the dosage taken.
- ③ Participants follow the investigator's instructions for the following evaluations:
  - Fatigue assessment using FSS.
  - Evaluate fatigue using the Chalder Fatigue Scale (ChFS).
  - Assess fatigue severity using a 0-100 VAS.
- ④ Prescribe a four-week supply of the clinical trial medication based on the random number.
- ⑤ Investigate concomitant medications.
- ⑥ Confirm any adverse reactions after taking the clinical trial medication.

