#### **11.4.1.4 Visit 4 (End of Intervention, Week 12 (84 days) $\pm 2$ days)**

During Visit 4, the administration of the clinical trial medication is completed, and the following tests are conducted, marking the end of the clinical trial.

- ① After collecting the prescribed herbal medicine from the previous visit, verify the dosage taken.
- ② Measure vital signs.
- ③ Conduct blood tests and ECG:
  - Blood chemistry : AST , ALT , BUN, creatinine
  - Electrocardiography: EKG
- ④ Collect blood samples for immune and metabolite tests:
  - Immunology: COVID-19 specific antibody/neutralizing antibody tests, single-cell transcriptome analysis (scRNA seq.) for immune-related gene expression comparison, FACS for immunophenotyping, serum cytokine levels.
  - Metabolomics: primary and secondary metabolite profiling.
- ⑥ Participants follow the investigator's instructions for the following evaluations:

- Fatigue assessment using FSS.
  - Evaluate fatigue using the Chalder Fatigue Scale (ChFS).
  - Assess fatigue severity using a 0-100 VAS.
  - Assess quality of life using EQ-5D-5L.
  - Evaluate sleep status using PSQI-K (Korean version of the Pittsburgh Sleep Quality Index).
  - Conduct cognitive function tests using K-MOCA (Korean-Montreal Cognitive Assessment).
  - Evaluate depression using Beck's Depression Inventory (BDI).
  - Perform digit span tests (forward and backward).
  - Conduct computerized neurocognitive function tests.
  - Perform the Short Physical Performance Battery (SPPB).
- ⑤ Investigate concomitant medications.
- ⑥ Confirm any new adverse reactions since the last visit and follow up on previously reported adverse reactions.
- ⑦ Conclude the study and provide guidance for any necessary follow-up visits.

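### Section 12.2 item 3 keeps a product-leaflet line telling participants in both arms to stop if symptoms do not improve within several days, which is inconsistent with the planned 12 weeks of dosing

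*Protocol*

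**What the plan says.** Protocol Section 12 gives precautions for the investigational products. Its only subsection is headed "12.2 CV1 (Jin Kyungok-go) and P (placebo"), so it covers both arms. Item 3 opens with "Discontinue this medication immediately and consult a doctor, herbal doctor, dentist, pharmacist, or herbal pharmacist if" and lists two triggers. The first is skin or digestive symptoms. The second is "Your symptoms do not improve after several days of taking the medication". The same item asks the reader to "bring this information leaflet when consulting".

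The treatment plan is stated elsewhere:

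- **11.1:** participants in either arm "will receive the respective intervention for 12 weeks".
- **11.4.1.2 (Visit 1):** "Prescribe a four-week supply of the assigned herbal medicine based on the random number".
- **11.4.1.3 (Visits 2 and 3):** a further four-week supply each time, with no condition on response.
- **11.4.1.4 (Visit 4):** dosing finishes; the heading reads "End of Intervention, Week 12 (84 days") with a window of ±2 days.
- **15.1.1:** the primary comparison is FSS between groups after 12 weeks of intervention.
- **Section 13:** seven conditions for discontinuing a participant. Lack of improvement is not one of them. Item 7 leaves other reasons to the researcher.

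**The concern.** The line makes stopping depend on whether fatigue improves, which is the outcome the trial measures. It gives no number of days and no criterion for improvement. A site or participant who followed it would stop the product long before week 12, and one who treated it as label text would continue. The protocol does not say which is intended.

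At stake is consistent handling of participants who do not respond early. Anyone who stopped on this ground and was not assessed again would have only the screening FSS, and 14.1 handles missing efficacy data by LOCF. Adherence, dropout and reasons for dropout are also secondary outcomes of this pilot (14.3.2), so stops prompted by a stray leaflet line would blur the feasibility results the trial is meant to supply.

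**Working it through.** The plan gives no figure to reproduce, so the check sets the sections side by side, with one piece of date arithmetic.

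**1. Is the line leaflet text?** Yes. It addresses the user as *you* and refers to an information leaflet. Neighbouring items deal with infants, dosing of children and spoons in a medication bottle. The trial enrols adults aged 19 and above (Section 7) and supplies stick pouches (9.1). The text was not adapted to the trial.

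**2. Does the protocol disapply it?** No. No sentence in Section 12 or 13 says that Section 12.2 is for information only or that Section 13 takes precedence. Some lines in 12.2 do fit the trial: the caution about overlapping herbal ingredients agrees with the restriction in 9.5. A reader therefore has to sort the section line by line.

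**3. Does it agree with the dosing plan?**

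| Topic | Section 12.2 item 3 | Elsewhere in the protocol |
|---|---|---|
| Duration | Stop if no improvement after several days | 12 weeks (11.1), 12 × 7 = 84 days |
| Continuation | Depends on improvement | Four-week supplies at Visits 1, 2 and 3, no improvement condition |
| Grounds for stopping | Lack of improvement | Not listed in Section 13; possible only through item 7 |
| Primary comparison | Not addressed | FSS after 12 weeks (15.1.1) |

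**4. When would the stop fall relative to FSS?** The Schedule Summary puts FSS at Visit 0 and then at Visits 2, 3 and 4. Visit 2 is day 28 ±2, so the earliest in-window on-treatment FSS is 28 − 2 = day 26. The protocol does not define *several days*. Any reading shorter than 26 days places the stop before the first scheduled on-treatment FSS. For an assumed range of 3 to 14 days, the gap is 26 − 3 = 23 days down to 26 − 14 = 12 days. The conclusion therefore does not depend on the exact reading.

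**5. What limits the loss of data?** Section 11.4.1.7 names early dropout as a reason for an unscheduled visit and asks for the Visit 4 tests as far as practicable. FSS is among them. This reduces the number of participants left with only a screening value, but it is not guaranteed.

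**The case against.** The best case against the point is that Section 13 carries the title of discontinuation and withdrawal criteria, while Section 12 is about precautions for use and is plainly consumer text. Most sites would apply Section 13 and ignore the leaflet line, as they would the advice about spoons. No route to participants is shown either: the label contents in 9.3 include no such instruction, and the document does not show any participant leaflet built from 12.2. Much of this stands, and it keeps the point small. It does not remove the inconsistency, because nothing in the protocol says the line does not apply.

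Two stronger readings are tempting but not supported:

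- **That the two instructions are logically incompatible.** Twelve weeks is a planned duration, and any stopping condition can sit alongside a planned duration. Section 13 item 7 would permit such a stop, and item 3 does not forbid resuming after the consultation.
- **That the skin and digestive triggers in item 3 conflict with 16.2(3).** That subsection is a list for recording what was done after an adverse event. It does not prescribe an action. Stopping and consulting for rash or digestive symptoms is a reasonable precaution and matches the predictable reactions in 16.2(5).

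**Conclusion.** The point holds as a minor internal inconsistency. It is pasted text that was not adapted, and should not be read as a deliberate design choice. Section 12.2 item 3 states a response-dependent stop for both arms that disagrees with 11.1, 11.4.1.3 and 15.1.1 and is absent from the conditions in Section 13.

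The timing statement, that a literal stop would precede the first on-treatment FSS, rests on reading *several days* as fewer than 26 days. A reader might go on to infer that the trial will lose participants or that FSS will be biased in a particular direction. The document gives no basis for that. It does not show how often the line would be followed, and the size and direction of any effect on FSS or dropout cannot be derived from it.

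**What to change.** Delete the non-improvement line from 12.2 item 3 and from any participant material taken from it, or state that it does not apply in this trial. Add two sentences: that Section 13 governs discontinuation, and that lack of improvement alone is not a protocol reason to stop the product before week 12, with the participant's right to withdraw at any time unchanged. Leave the skin and digestive stop-and-consult precautions as they are.

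The cost is a short wording amendment, with the IRB approval that 20.4 requires for any protocol change. It needs no extra visits, tests or participants.
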